## 7 SELECTION AND WITHDRAWAL OF SUBJECTS

### 7.1 INCLUSION CRITERIA

1. Subject included in ChAd-MVA.HIVconsv\_BCN01 study with complete follow-up and included in BCN01-RO extension study.
2. Willing and able to give written informed consent for participation in the study
3. Willing and able to keep a good adherence to their cART regimen for the duration of the intervention phase.
4. Optimal virological suppression for at least 3 years defined as maintained pVL below limit of detection (based on current available assays, 20 or 40 copies/ml) allowing for isolated blips (<200 cop/ml, non-consecutive, >10% total determinations).
5. Being on a non-boosted integrase-inhibitor based regimen (raltegravir or dolutegravir) for at least 4 weeks at screening visit.
6. No new AIDS-defining diagnosis or progression of HIV-related disease.
7. Haematological and biochemical laboratory parameters as follows:
  - a. Haemoglobin > 10g/dl
  - b. Platelets > 100.000/dl
  - c. ALT ≤ 2.5 x ULN
  - d. Creatinine ≤ 1.3 x ULN
8. Serology: negative for hepatitis B surface antigen; negative for hepatitis C antibodies OR confirmed clearance of HCV infection (spontaneous or following treatment).
9. Available for follow up for duration of study (baseline + at the most 54 weeks) and willing to comply with the protocol requirements
10. Age ≥18 years
11. CD4 T cell count ≥500 cells/mm^3

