## 7.3 SUBJECT WITHDRAWAL CRITERIA

### 7.3.1 Related to MVA.HIVconsrv vaccination

First MVA.HIVconsrv vaccination will only be administered if plasma viral load (pVL) is below the limit of detection in 2 consecutive determinations and CD4 cell count > 500 cells/ml at baseline. After RMD administration, low-level viral load detections (pVL<2,000 copies/ml) will be allowed only if suboptimal cART adherence is not suspected.

Any individual for who is being considered for discontinuation or postponement of vaccinations will be discussed with the trial team.

Participants might be discontinued or postponed -if clinical condition or laboratory abnormality is resolved within a maximum window of 10 days- from further vaccination for any of the following reasons:

- Ineligibility (either arising during the study or retrospective having been overlooked at screening).
- A disease, condition or an adverse event (including clinically significant abnormal laboratory values; see below) that develops, regardless of relationship to the study products, if, in the opinion of the principal investigator or designee, further vaccinations would jeopardize the safety of the patient.
- Hematology
  - Hemoglobin < 10.0 g/dl
  - Absolute Neutrophil Count (ANC)  $\leq 1000 /\text{mm}^3$  ( $\leq 1 \times 10^9 /\text{l}$ )
  - Absolute Lymphocyte Count (ALC)  $\leq 600 /\text{mm}^3$  ( $\leq 1 \times 10^9 /\text{l}$ )
  - Platelets  $\leq 50.000 /\text{mm}^3$ ,  $\geq 550,000 /\text{mm}^3$  ( $\leq 50 /\text{L}$ ,  $\geq 550 /\text{L}$ )
- Biochemistry

- Creatinine > 1.3 x ULN
  - AST > 2.5 x ULN
  - ALT > 2.5 x ULN
- Confirmed HIV-1 or HIV-2 re-infection.
- Pregnancy.
- Significant non-compliance with cART regimen or study requirements.
- Receipt of blood transfusion or blood products during this study.
- Participating in another clinical trial of an IMP.
- A serious adverse event judged to be possibly, probably or definitely related to vaccination.
- An adverse event which requires discontinuation of the study product or results in inability to continue to comply with study procedures.
- Loss to follow up.
- The safety of the volunteer would be jeopardized in the opinion of the investigator or sponsor.
- Investigator discretion.
- Significant protocol deviation.

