### 7.3.3 Related to cART interruption

As persistent detectable viral replication may induce immune activation that could favor a faster viral rebound after cART cessation, cART interruption will only be indicated if plasma viral load (pVL) is below the limit of detection in 2 consecutive determinations, spaced at least 1 week, at MAP visit (MVA2+8w). In case that MVA.HIVconsv second booster immunization may induce repetitive detectable plasma HIV-1 RNA determination still present at MAP visit, cART interruption will be postponed until 2 consecutive determinations are achieved.

Any individual for who is being considered for postponement of cART interruption will be discussed with the trial team.

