#### **8.1.14 MAP – Monitored antiretroviral pause and MVA2+8w – Eight weeks post MVA2 vaccination (17 weeks)**

Following procedures will be performed at both clinical sites (HGTIP and HC):

- Blood extraction including:
  - Viral load, biochemistry and hematological parameters.
  - Plasma and PBMC storage following scheme detailed in attachment K
- cART adherence assessment (SERAD questionnaire)
- Clinical visit, adverse event register
- Review acceptability for cART interruption after interim analyses (which will be performed at week 13 and be provided by investigational team in advance and recorded in 'Indication for MAP phase' form, attachment X)
- Review acceptability for cART interruption regarding plasma viral load suppression (pVL below the limit of detection in 2 consecutive determinations, spaced at least 1 week, and recorded in 'Indication for MAP phase' form, attachment X)
- Phase 2 study explanation including: cART interruption, site, weekly clinical visit, qualitative plasma viral load monitoring, criteria for cART resumption.
- CRF data collection

Once analytical results are available, cART interruption will be confirmed telephonically by study physician and first visit in BCN-Checkpoint will be scheduled.

In cases where pVL is not undetectable for 2 consecutive determinations, MAP will be postponed and extra visits will be scheduled (every week if pVL is 20-500 copies/mL, every two weeks if pVL is >500 copies/mL) including the following procedures until acceptability criteria for cART interruption are met.

- Blood extraction including:
  - Viral load, biochemistry and hematological parameters.
  - Plasma and PBMC storage.
- cART adherence assessment (SERAD questionnaire)
- Clinical visit, adverse event register

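### The blip allowance in inclusion 4 is printed as a floor instead of a ceiling, and the lymphocyte hold in 7.3.1 and 7.3.2 equates two unequal counts

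*Protocol*

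**What the plan says.** Protocol section 7.1, inclusion criterion 4, requires at least three years of viral load kept below the detection limit, "allowing for isolated blips (<200 cop/ml, non-consecutive, >10% total determinations".

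Sections 7.3.1 (vaccination) and 7.3.2 (romidepsin) each list haematology values that are grounds to withhold further doses. In both, the absolute neutrophil count (ANC) line gives ≤1000/mm³ with ≤1 × 10⁹/l in brackets. The ALC line below it gives ≤600/mm³ with the same bracket, ≤1 × 10⁹/l. The lists are introduced by "Participants might be discontinued or postponed", and each case under consideration is to be discussed with the trial team.

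Inclusion 7 ("Haematological and biochemical laboratory parameters as follows") covers haemoglobin, platelets, ALT and creatinine and sets no lymphocyte limit. The laboratory list in 8.4.2 names lymphocytes without a threshold.

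**The concern.** The first two terms in the blip bracket, a size cap and a ban on consecutive blips, are restrictions. The third should restrict too, but as printed it applies the allowance only to people whose blips exceed a tenth of their determinations. That conflicts with the words optimal and isolated in the same criterion.

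The ALC line states two different limits as one. A physician reading the first half of the line and a physician reading the bracket would disagree on whether a count of, say, 800/mm³ is a listed reason to hold a dose. The lists are used in practice: prescribing the first vaccination depends on the vaccination criteria being met (8.1.2), they are reviewed again before the second (8.1.11), and laboratory results are reviewed before each romidepsin prescription (8.1.4, 8.1.6, 8.1.8). Postponement is limited to 10 days for vaccine and 7 days for romidepsin, and participants cannot be replaced (7.3.7).

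At stake is the correct statement of one entry rule and one hold rule. No sample size, test or endpoint depends on either.

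**Working it through.** **ALC hold.** Inputs: the ANC and ALC lines of 7.3.1, repeated in 7.3.2. Conversion: 1 l = 10⁶ mm³, so count per litre = count per mm³ × 10⁶.

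- ANC, as a check on the conversion: 1000 × 10⁶ = 1.0 × 10⁹/l. The bracket agrees.
- ALC: 600 × 10⁶ = 0.6 × 10⁹/l. The bracket says 1 × 10⁹/l, which is 1,000/mm³. It does not agree.
- Ratio of the two limits: 1,000 / 600 = 1.67.
- Counts meeting one limit but not the other: 601 to 1,000/mm³, a band of 1,000 − 600 = 400 cells/mm³.

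The identical bracket on the line above, where it is right, suggests that it was copied down.

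**Blip allowance.** Inputs: the three conditions in inclusion 4. Let k be the number of blips and n the number of determinations. The Protocol gives no n, so the values below are assumptions. Only candidates whose blips are all <200 copies/ml and non-consecutive are counted; with no two in a row, k is at most (n + 1)/2 rounded down. As printed, k/n > 0.10; corrected, k/n < 0.10 or ≤ 0.10.

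| Assumed n | Non-zero k allowed as printed | Non-zero k allowed under a 10% ceiling |
|---|---|---|
| 6 | 1–3 | none |
| 12 | 2–6 | 1 |
| 24 | 3–12 | 1–2 |

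For n = 12: 1/12 = 8.3% fails as printed, while 2/12 = 16.7% through 6/12 = 50% pass. At these three values of n, < and ≤ give the same answer. They differ only at exactly 10%: 1 blip in 10 passes under ≤10% but fails under <10%, and it also fails as printed. A single blip is rejected by the printed rule only when n is 10 or more (1/9 = 11.1% passes, 1/10 = 10.0% does not). With fewer determinations, the printed rule errs only by admitting blips that a ceiling would exclude.

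**Clerical unit slips nearby.**

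- Inclusion 7b reads "Platelets > 100.000/dl"; 1 dl = 100,000 mm³, so 100,000/dl would be 1/mm³.
- Section 7.3.1 requires "CD4 cell count > 500 cells/ml at baseline"; 1 ml = 1,000 mm³, so that would be 0.5/mm³, whereas inclusion 11 has "CD4 T cell count ≥500 cells/mm"³.
- The platelet hold brackets give 50 and 550 per litre without the factor 10⁹; with it, 50 × 10⁹/l = 50,000/mm³ and 550 × 10⁹/l = 550,000/mm³, which match the first values.

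The intended unit is obvious in each case.

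**The case against.** The strongest reply is that neither slip is likely to misdirect anyone. The direction of the blip limit is clear from its own sentence, and the investigators are choosing among at most 24 people whom they already follow. The ALC line is a prompt for discussion: the lists also include investigator discretion and jeopardised safety, so a count of 601–1,000/mm³ can be held or dosed under either value. Viral load is checked again regardless of inclusion 4. The first vaccination needs two consecutive undetectable results (7.3.1). Treatment interruption is indicated only if viral load is "below the limit of detection in 2 consecutive determinations, spaced at least 1 week, at MAP visit", and 8.1.14 repeats the check ("Review acceptability for cART interruption regarding plasma viral load suppression"). All of this stands, and it is why the point is minor. It does not make the printed text right: the hold list is what prompts the discussion, and it should give one value.

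Three stronger readings are tempting and are not supported.

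- A reader might infer that the printed sign reverses the decision for every candidate who has had a blip. It does not: blips of 200 copies/ml or more, or consecutive ones, fail under both readings, and at exactly 10% the result depends on whether < or ≤ was meant.
- A reader might conclude that nothing in the trial's papers settles the ALC limit. The prescription forms and the CRF content are attachments that are not shown, so only the visible text can be said to leave it open.
- A reader might treat the ALC line as a binding dosing limit. Its wording is permissive.

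A symbol lost in reading the PDF cannot be fully excluded for the blip sign, but the < before 200 in the same bracket came through correctly. The ALC mismatch appears identically in two sections.

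**Conclusion.** Both errors stand, at minor severity. The blip limit is a floor where a ceiling is evidently intended. Its literal effect is confined to candidates whose blips otherwise qualify, and the illustrative counts rest on assumed numbers of determinations. The two ALC limits differ by a factor of 1.67, which leaves the status of counts from 601 to 1,000/mm³ contradictory for both products. That 600/mm³ is the intended value is a reasonable presumption from the ANC line, but the Protocol does not say so. No efficacy or safety analysis is affected. The platelet and CD4 unit slips are clerical, and no effect is attributed to them.

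**What to change.** In inclusion 4, replace >10% with a ceiling, <10% or ≤10% of total determinations, with the sponsor confirming which. In 7.3.1 and 7.3.2, state one ALC limit, presumably ≤600/mm³ (≤0.6 × 10⁹/l), once the clinical team confirms it. Check that the prescription forms carry the same value.

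The same amendment can correct the units: platelets >100,000/mm³ in inclusion 7b; ≤50 and ≥550 × 10⁹/l in the platelet hold brackets; and cells/mm³ for the CD4 requirement in 7.3.1.

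The cost is amendment wording and any matching eCRF edit checks, with no new visits, samples or procedures. On the planned calendar (first visit February 2016, six months of inclusion), this version, dated 30 May 2016, already falls in the second half of enrolment. The entry correction would therefore reach only later candidates, and the ALC correction only doses still to be given.

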### 7.2 EXCLUSION CRITERIA

1. Confirmed HIV-2 seropositive
2. Positive pregnancy test. \*
3. Presence of resistance drug mutations in the screening genotype \*\*
4. Participation in another clinical trial within 12 weeks of study entry
5. History of autoimmune disease other than HIV-related auto-immune disease.
6. History or clinical manifestations of any physical or psychiatric disorder which could impair the subject's ability to complete the study.
7. History of anaphylaxis or severe adverse reaction to vaccines.
8. Previous immunisation with any experimental immunogens (except for ChAd.HIVconsv and MVA.HIVconsv)
9. Receipt of blood products within 6 months of study entry
10. Treatment for cancer or lymphoproliferative disease within 1 year of study entry
11. Receipt of vaccines within 2 weeks of study entry and along the duration of the trial
12. Any other prior therapy which, in the opinion of the investigators, would make the individual unsuitable for the study or influence the results of the study

13. Current or recent use (within last 3 months) of interferon or systemic corticosteroids or other immunosuppressive agents

\* Female subjects of childbearing potential must not be pregnant, not be planning a pregnancy or breast-feeding. Sexually active women must be willing to use two approved methods of contraception (including condoms, diaphragm, spermicides, hormonal methods and/or intrauterine devices) from screening until 28 days after last immunization. Sexually active men in heterosexual relationships must be willing to use two approved method of contraception with their partners from screening until 28 days after last immunization.

\*\* Pre-cART genotype (performed at BCN01 screening visit)

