### 7.3.2 Related to romidepsin administration

Any individual for who is being considered for discontinuation or postponement of RMD administrations will be discussed with the trial team.

Participants might be discontinued or postponed -if clinical condition or laboratory abnormality is resolved within a maximum window of 7 days- from further romidepsin administration for any of the following reasons:

- Ineligibility (either arising during the study or retrospective having been overlooked at screening).
- A disease, condition or an adverse event (including clinically significant abnormal laboratory values; see below) that develops, regardless of relationship to the study products, if, in the opinion of the principal investigator or designee, further vaccinations would jeopardize the safety of the patient.
- Hematology
  - Hemoglobin < 10.0 g/dl
  - Absolute Neutrophil Count (ANC)  $\leq 1000 /\text{mm}^3$  ( $\leq 1 \times 10^9 /\text{l}$ )
  - Absolute Lymphocyte Count (ALC)  $\leq 600 /\text{mm}^3$  ( $\leq 1 \times 10^9 /\text{l}$ )
  - Platelets  $\leq 50.000 /\text{mm}^3$ ,  $\geq 550,000 /\text{mm}^3$  ( $\leq 50 /\text{L}$ ,  $\geq 550 /\text{l}$ )
- Biochemistry
  - Creatinine > 1.3 x ULN
  - AST > 2.5 x ULN
  - ALT > 2.5 x ULN
- Confirmed HIV-1 or HIV-2 re-infection.
- Pregnancy.
- Significant non-compliance with cART regimen or study requirements.
- Receipt of blood transfusion or blood products during this study.
- Participating in another clinical trial of an IMP.
- A serious adverse event judged to be possibly, probably or definitely related to romidepsin administration.
- An adverse event which requires discontinuation of the study product or results in inability to continue to comply with study procedures.
- Loss to follow up.
- The safety of the volunteer would be jeopardized in the opinion of the investigator or sponsor.
- Investigator discretion.

- Significant protocol deviation.
- Disease progression, including virological failure (defined as a rebound in at least two consecutive determinations of pVL > 2,000 copies/ml after suppression), which requires discontinuation or modification of the study medication or results in inability to continue to comply with study procedures. Low-level pVL determinations just after vaccinations and/or during RMD administration will be allowed only if suboptimal cART adherence is not suspected.
- Consent withdrawn.

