### 7.3.4 Early subject withdrawal

The patients will complete the clinical study before the stipulated time in the following circumstances:

- Concurrent process or illness which in the opinion of the investigator requires the withdrawal of the patient.
- Protocol deviation which in the opinion of the sponsor requires the withdrawal of the patient.
- The patient does not wish to continue in the study.
- Other

On the other side and in order to minimize risks of the treatment interruption intervention, an early interim and futility analyses is planned before the MAP phase for each individual. Treatment interruption would be discouraged if boosting MVA.HIVconsv is shown to be no longer immunogenic after romidepsin administration –defined as no net increase of HIVconsv-specific IFN $\gamma$  response compared to pre-vaccination levels with MVA.HIVconsv at BCN02-Romi baseline visit, due to RMD toxicity on CTL functional

activity for instance, as an improved viral control would not be foreseen. These results are considered valid for up to 12 weeks from the second vaccination. As vaccine induced T-cells may decrease in the following weeks and available data on expected kinetics of immune response is limited, in the event that the cART interruption is postponed more than MVA2 + 12w, the futility analyses should be repeated and results will be discussed among the investigators

In such situation, trial results would be focused on the viral reservoir and immunogenicity endpoints only until better correlates of control would be available to predict clinically relevant outcomes on which one could recommend treatment interruptions in a safer manner.

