## 9.6 FEMALES OF CHILDBEARING POTENTIAL

Pregnancies and suspected pregnancies (including a positive pregnancy test regardless of age or disease state) of a female subject occurring while the subject is on romidepsin or MVA.HIVconsv, or within 28 days of the subject's last dose of romidepsin or MVA.HIVconsv, are considered immediately reportable events. Romidepsin or MVA.HIVconsv is to be discontinued immediately and the subject instructed to return any unused portion of romidepsin or MVA.HIVconsv to the Investigator. The pregnancy, suspected pregnancy, or positive pregnancy test must be reported to the Sponsor who, in case patient was exposed to romidepsin, will inform Celgene immediately using the Pregnancy Reporting Form provided by Celgene or an approved equivalent form.

Romidepsin may have reproductive toxicity if taken during pregnancy. In case the female subject was exposed to romidepsin, she should be referred to an obstetrician-gynecologist, preferably one experienced in reproductive toxicity for further evaluation and counseling.

The Investigator will follow the female subject until completion of the pregnancy, and must notify the Sponsor immediately about the outcome of the pregnancy (either normal or abnormal outcome).

If the outcome of the pregnancy was abnormal (e.g., spontaneous or therapeutic abortion), the Investigator should report the abnormal outcome as an AE. If the abnormal outcome meets any of the serious criteria, it must be reported as an SAE within 24 hours of the Investigator's knowledge of the event using the SAE Report Form, or approved equivalent form.

All neonatal deaths that occur within 28 days of birth should be reported, without regard to causality, as SAEs. In addition, any infant death after 28 days that the Investigator suspects is related to the in utero exposure to the IP should also be reported within 24

hours of the Investigator's knowledge of the event using the SAE Report Form, or approved equivalent form.

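### Contraception in 7.2 is tied only to the last vaccination, so a participant who stops after romidepsin and before MVA2 has no requirement counted from the last infusion

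*Protocol*

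**What the plan says.** The starred footnote to Protocol 7.2 sets the contraception period. For women, two approved methods are required, with the list of methods and the period ending "hormonal methods and/or intrauterine devices) from screening until 28 days after last immunization". Men in heterosexual relationships "must be willing to use two approved method of contraception with their partners from screening until 28 days after last immunization".

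Section 6.1 lists two investigational products: MVA.HIVconsv, described as a vaccine, and romidepsin. The vaccine is given at weeks 0 and 9 (6.3.2) and romidepsin at weeks 3, 4 and 5 (6.3.1).

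Section 9.6 warns: "Romidepsin may have reproductive toxicity if taken during pregnancy". It adds: "In case the female subject was exposed to romidepsin, she should be referred to an obstetrician-gynecologist". For reporting, the same section counts from either product: pregnancies on treatment "or within 28 days of the subject's last dose of romidepsin or MVA.HIVconsv, are considered immediately reportable events". Sections 7.3.6 and 9.2 likewise count 28 days from the last dose of investigational product when collecting adverse events after early withdrawal on treatment.

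The protocol provides for stopping between the products:
- 7.3.1 allows discontinuation or postponement, the latter if a problem is "resolved within a maximum window of 10 days- from further vaccination for any of the following reasons".
- 7.3.2 stops further romidepsin for, among other reasons, "A serious adverse event judged to be possibly, probably or definitely related to romidepsin administration".
- 7.3.4 ends participation early when "The patient does not wish to continue in the study".
- 5.6 suspends the study, pending review, after two or more clinically similar related serious or grade 3 events.

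**The concern.** The rule follows one product and the warning follows the other. Romidepsin lies between the two vaccinations, so the vaccine anchor covers it only if the second vaccination is given. Once MVA2 is no longer due, the last immunization is MVA1 at week 0 and nothing in 7.2 refers to the infusions received since.

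The pregnancy tests before each infusion (8.1.4, 8.1.6, 8.1.8) guard against dosing a woman who is already pregnant. They do not bear on conception after the last infusion. During the following 28 days, section 9.6 still makes a pregnancy immediately reportable and refers a romidepsin-exposed woman to a specialist, yet an early stopper has no stated duty to avoid one. The visit lists after the third infusion (8.1.9 to 8.1.11) name no further pregnancy test.

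What is at stake is participant safety. No endpoint or analysis is affected.

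**Working it through.** The protocol states no figure to reproduce. The check is schedule arithmetic in weeks, with 28 days = 4 weeks.

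**Inputs**
- MVA1 at week 0 and MVA2 at week 9 (6.3.2)
- Infusions RMD1, RMD2 and RMD3 at weeks 3, 4 and 5 (6.3.1)
- Contraception ends 4 weeks after the last immunization (7.2)
- Benchmark: 4 weeks after the last romidepsin dose, borrowed from the pregnancy-reporting window in 9.6

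**Planned schedule**
- Contraception ends at week 9 + 4 = week 13.
- Time covered after RMD3 = 13 − 5 = 8 weeks, twice the benchmark. There is no gap.

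**Stopping before MVA2**

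Let L be the week of the last infusion and d the week of the decision to stop, with d ≥ L. Until d, MVA2 is still expected, so contraception is assumed to continue. The MVA1 anchor alone runs to week 0 + 4 = week 4. The benchmark ends at L + 4. Hence:

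uncovered weeks = max(0, (L + 4) − max(4, d))

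| Last infusion | d = 3 | d = 4 | d = 5 | d = 6 | d = 7 | d = 8 | d = 9 |
|---|---|---|---|---|---|---|---|
| RMD1 (L = 3, benchmark ends week 7) | 3 | 3 | 2 | 1 | 0 | 0 | 0 |
| RMD2 (L = 4, benchmark ends week 8) | – | 4 | 3 | 2 | 1 | 0 | 0 |
| RMD3 (L = 5, benchmark ends week 9) | – | – | 4 | 3 | 2 | 1 | 0 |

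For example, RMD3 last with a decision at week 6 gives (5 + 4) − max(4, 6) = 3 weeks. Since d ≥ L, the result can never exceed (L + 4) − L = 4 weeks. It reaches zero for someone who drops out only at the week 9 check before MVA2.

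**Stricter reading**

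If the requirement is taken, in retrospect, to have ended at week 4 whatever was still planned, the RMD3 case runs from week 4 to week 9, which is 5 weeks. If RMD3 was postponed by the 7 days that 7.3.2 allows, it runs from week 4 to week 10, which is 6 weeks. Four of those weeks follow the last infusion in either case.

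**With the anchor moved to the last dose of either product**

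An early stopper would be covered to week 3 + 4 = 7, 4 + 4 = 8 or 5 + 4 = 9. Anyone who receives MVA2 stays at week 13.

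**The case against.** The strongest reply is that the rule works as designed: on schedule it gives 8 weeks of cover after the last infusion. That is correct, and it confines the point to early stoppers.

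Second, a romidepsin-related serious adverse event under 7.3.2 stops further romidepsin. It does not by itself cancel MVA2, and the matching item in 7.3.1 concerns events related to vaccination. This also stands. Such an event opens the gap only if vaccination is ended too, for example at the investigator's discretion under 7.3.1. The route remains open through 7.3.1, through withdrawal by choice under 7.3.4, and through a suspension under 5.6 that becomes permanent.

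Third, the 28-day benchmark comes from reporting and follow-up rules, which are not contraception rules. The warning speaks of exposure during pregnancy, and no text shown states a risk from later conception or to partners of male participants. This stands as a limit on what can be said about harm, and it is why the point is a gap and not a contradiction. It does not explain why 7.2 should follow the vaccine alone.

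Fourth, the silence on later pregnancy tests is weak evidence. Attachment J holds the detailed schedule, 8.4.2 lists the test among those done as needed, and 7.3.6 asks for the tests of the visit on early discontinuation. That is fair, but a test detects pregnancy and does not prevent it.

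Finally, wording in an eligibility footnote can hardly be enforced on someone who has left. It does, however, set the commitment given at consent and the advice given on leaving.

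**Conclusion.** The concern holds. Section 7.2 fixes the end of contraception by the wrong event: followed as written, it leaves a participant who stops after romidepsin and before MVA2 with no requirement counted from the last infusion of the only product that carries a reproductive warning in the text shown.

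The gap is small: at most 4 weeks, shrinking by a week for each week the decision comes later, and nil for anyone who receives MVA2. At most 24 participants enrol (10.3). The protocol gives neither the number of women nor an expected number of such stops, so no count of those affected can be offered.

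The size rests on two assumptions: that contraception continues until the decision to stop, and that 28 days is the right period for romidepsin. A longer required period would widen the gap. Attachments J (schedule), R (patient information and consent) and T (romidepsin brochure) are not shown and may say more. If they already cover this, 7.2 should still agree with them. The change should be made, although it is not critical to the trial.

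**What to change.** In both sentences of the 7.2 footnote, end the contraception period 28 days after the last dose of MVA.HIVconsv or romidepsin, whichever is later, or later still if the romidepsin product information requires it. Align the consent wording in Attachment R.

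As a secondary step, apply the same window to partner pregnancies in 9.6.1, which now asks men to report them only during treatment, without the 28 days used for women in 9.6.

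The cost is one phrase changed in two places, matching consent text and, optionally, one sentence in 9.6.1. With the 28-day figure, nobody who receives MVA2 has a longer contraception period than now.
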